### **12.3 Data sharing**

Data will be shared between GSTFT and KCL in adherence with the Data Protection Act 2018. A data transfer agreement will be established to allow for transfer of data collected by therapists at GSTFT to the research team at KCL. Therapists at GSTFT involved in recruitment and intervention delivery are responsible for the collection of this data, its recording and quality. Participants will be required to consent to this data transfer prior to enrollment in the trial.

Identifiable data will be collected in REDCap hosted by the Trust (GSTFT) or a password protected file on a secure KCL SharePoint server for those who provide informed consent. The database will be accessible by the therapists at GSTFT and authorized members of the research team to arrange telephone assessments, telephone/MS TEAMS interviews, to send the trial results by post (if a participant selects this option), and to send patient-reported outcome measures by post for participants who are non-English language speakers, this database will specify the participant identification number.

Pseudo-anonymised screening, eligibility, approach, randomisation and allocation, and treatment logs will be entered by therapists to a REDCap database. The database will be pseudo-anonymised with the use of the patient identification number as the primary identifier of the participant for data entered. The database will be accessible by the therapists at GSTFT and authorized members of the research team at KCL for analysis.

### **12.4 Personal Data Breaches**

Personal data breaches are defined as a security incident that has affected the confidentiality, integrity, or availability of personal data. In short, there will be a personal data breach whenever any personal data is lost, incorrectly destroyed, corrupted, or disclosed; if someone accesses the data or passes it on without proper authorization; or if the data is made unavailable, for example, when it has been encrypted by ransomware, or accidentally lost or destroyed.

Personal data breaches will be immediately reported to the CI, Sponsor's, and to the Data Protection Officer/Information Governance Department of the site that incurred the breach. The report will include full details as to the nature of the breach, an indication as to the volume of material involved, and the sensitivity of the breach (and any timeframes that apply), steps that have been taken to mitigate the risk (trying to retrieve the data asking third parties to delete information that was sent to them in error) to enable an assessment of the full risk/impact of the breach. The Sponsor will determine whether the breach meets the definition of a serious breach and warrants reporting to the regulators including the ICO <https://ico.org.uk/for-organisations/report-a-breach/personal-data-breach-assessment/>.

Sites will additionally follow their Trust incident reporting mechanisms and will document this within their trial master file in the form of a file note provided by the sponsor with Corrective and Preventative Actions addressed.

## **13 MONITORING AND AUDITING**

The Chief Investigator will be responsible for the ongoing management of the study. The Sponsor will monitor and conduct audits on a selection of studies in its clinical research portfolio. Monitoring and auditing will be conducted in accordance with the UK Policy Framework for Health and Social Care and in accordance with the Sponsor's monitoring and audit procedures.

### ***13.1 Stopping / discontinuation rules and breaking of randomisation code***

The trial completion is the date when all data queries are resolved, and database locked which is anticipated to be month 15 from study start. There are no criteria for premature discontinuation of the trial (as a feasibility trial). There are no anticipated circumstances under which the randomisation codes may need to be broken.

### ***13.2 Monitoring, quality control and assurance***

The trial will be conducted in compliance with the approved protocol, the Declaration of Helsinki (2008), the principles of Good Clinical Practice (GCP) as laid down by the Commission Directive 2005/28/EC with implementation in national legislation in the UK by Statutory Instrument 2004/1031 and subsequent amendments, the UK Data Protection Act, and the UK Policy Framework for Health and Social Care Research, the Mental Capacity Act 2005, and other national and local applicable regulations.

The trial will be led and managed by the CI with the support of the trial manager. This will include co-ordination of all day-to-day aspects of the trial from initial set-up to closeout, including: development of the systems, protocol and other essential documents; REC/HRA submission and amendments; set-up and management of trial management group (TMG) and TSDMC meetings; planning and provision of site initiation visit; day-to-day liaison with site; study monitoring oversight; safety management and reporting, progress reporting to REC, TSDMC, Sponsor and funder; performance of site closure at end of study; provision of end of study notifications to HRA and REC; preparation of files for archiving.

The CI will chair the TMG, which will also include the investigators, PPI representative, trial manager, and trial statisticians meeting at least bi-monthly throughout the trial and more frequently during the earlier phases. The TMG will closely monitor study progress, identifying and addressing practical, scientific, and financial issues as they arise. The TMG will report progress to the Sponsor and the independent TSDMC.

The TSDMC will include the CI and trial manager, as well as an independent Chair, statistician, PPI representative, clinicians, and health services researchers. The committee will provide advice, data monitoring, quality assurance, and safety monitoring. The committee may include open and closed sessions. Closed sessions will not be attended by the chief investigator or trial manager and may be used for data monitoring and/or other discussions at the discretion of the Chair.

The research team will monitor treatment logs completed by treating therapists after each session against the treatment allocation and explore any quality control issues with treating therapists. Additionally, any quality control issues identified during treatment observations will be explored with the treating therapists.

The trial database will be programmed to generate notifications for possible data entry errors and missing key data points.

Prior to publication, the presentation of results (text, tables and figures) will be reviewed by the trial management group to ensure the anonymity of participants will be preserved. In particular, we will review variable level counts and identify any which are small and in combination with other data could render information potentially identifiable. If this occurs, we will categorize the variable further to ensure anonymity is preserved. If further categorization is not possible, we will suppress the potentially identifiable data and report the extent to which data suppression was employed in the results.

## **14 STATISTICAL CONSIDERATIONS**

### **14.1 *Sample size***

The sample size was determined in consultation with the trial statistician. The recruitment target of 60 participants aims to have sufficient participants to provide the operational experience to plan a definitive trial; provide reasonably robust estimates of our feasibility outcomes; and to estimate the variability of the proposed patient outcomes to inform a future sample size calculation. A recruitment target of 60 participants (30 per treatment arm) will allow overall retention rate at 12-weeks to be estimated with precision of  $\pm 11\%$ , using an exact 95% confidence interval, from previously observed retention rates of  $\sim 80\%$  for the same population. Assuming a non-differential retention rate of 80% at 12-week follow-up, this target will provide follow-up outcome data on  $\sim 24$  participants per arm.

This required sample size will be attainable in practice. In 2022, 255 patients were admitted to a hospital ward at St Thomas's Hospital with hip fracture. Previous trials of patients with hip fracture reported recruitment rates of 32% in hospital.

## **14.2 Analysis plan**

A statistical analysis plan will be finalised ahead of database locking and reporting will follow the CONSORT guidance for pilot and feasibility studies. All analysis will select participants according to the principles of intention to treat.

## **14.3 Quantitative analysis**

A CONSORT flow diagram will display data specifying counts of screened, eligible, approached, randomised, and completed enabling estimation of eligibility, recruitment, consent and follow-up rates. Confidence intervals for recruitment and retention rates will be produced to inform assumptions for planning the definitive trial. Rates of screened, eligible, approach and recruited will also be estimated for carers of participants enrolled into the medium- or high-risk intervention arm. Completion rates will be estimated for outcome measures collected at each time-point. Baseline characteristics will be summarised by allocated arm (and by subgroup assignment) with descriptive statistics (measures of central tendency and dispersion) to enable assessment of baseline comparability of arms (a degree of imbalance is anticipated in this small feasibility study). Patient-reported outcomes and treatment fidelity will be summarised by allocated arm (and by subgroup assignment) at each follow-up, with descriptive statistics (measures of central tendency and dispersion). Between-arm differences, including in changes from baseline, will be reported for the patient-reported outcomes with corresponding measures of dispersion to enable an assessment of sensitivity to change to inform primary outcome selection for a definitive trial and a formal power calculation for this outcome for a definitive trial.

For patients who do not speak English, the count of pseudo-anonymised patient-reported outcome measures circulated and returned by post will be documented. The content of the patient-reported outcome measure will be described narratively ensuring participant anonymity is preserved (the language versions circulated will not be specified in reporting).

The quantitative analysis will be completed by a trial statistician using R (<https://www.r-project.org/>) (or other well validated statistical packages) after database lock at trial end. The TSDMC will monitor screening/eligibility, approach and randomisation rates and safety reporting. There are no additional interim analyses planned. Qualitative analysis

Qualitative data transcribed verbatim from semi-structured interviews and analysed using a thematic analysis approach. The analysis will follow a deductive approach informed by the categories of treatment fidelity (design, training of providers, delivery, receipt and enactment), and to identify barriers and/or facilitators (inclusive of acceptability) to future implementation.

The intervention observations will be sampled against therapists logs to further assess fidelity. Free text entries made during observations will be summarised narratively.

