## **7.4 Randomisation procedures**

The randomisation approach was designed with a statistician (SA) and validated for use prior to implementation. Once a participant has provided informed consent, they will be allocated a participant identification number (PID). Baseline data will subsequently be collected by the research team prior to randomisation. Randomisation will follow a 1:1 random allocation sequence stratified by subgroup assignment (low-, medium-, high- risk), using a secure internet-based system, developed and maintained by King's Clinical Trials Unit to ensure allocation concealment. Treatment allocation will be revealed (after randomisation) to a member of the research team, linked to the participant number, and the clinical team will be notified.

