## **12 DATA**

### ***12.1 Data collection***

Data collection, including who the data are to be collected by, from where, the data type and the time point for collection, is outlined in Table 2. Data collection at baseline and intervention end will be in-person or over the telephone/MS TEAMS (the mode will be documented). Assessments at 12-weeks post-randomisation will be completed over the telephone or MS TEAMS.

The following participant characteristics will be collected to enable baseline comparison: age, sex, fracture type, surgery type, Abbreviated Mental Test, Mini Nutritional Assessment, hospital concerns about falls, prefracture residential status, living status, prefracture mobility. The acceptability, completeness, and descriptive comparison of patient reported outcome data collection (secondary objective 4) will be assessed through collection of patient-reported outcome measures (via standardised tools) which satisfy the core outcome set for hip fracture trials. Additional patient-reported outcome measures (via standardised tools) which capture putative mechanisms (falls related self-efficacy, walking ability) for an effect on health-related quality of life (as the proposed outcome for a definitive trial) will also be collected.

Additional quantitative outcomes captured will include length of stay, death, readmissions, place of residence and living status (to determine if change to higher level of care, including informal care (e.g., living status change from alone to with family)) as key performance indicators of care after hip fracture surgery; and resource use using a bespoke data collection form to assess feasibility of collecting health economic data while minimising the burden on patients.

For patients who do not speak English, patient-reported outcome measures which have an established translated, validated, and (where applicable) culturally adapted version in the appropriate language will be circulated by post to the participant with a pre-paid envelope for return. Patient characteristics and additional quantitative outcomes will be collected using language support at the Trust.

For carers recruited to the study, we will collect data relating to their age, sex, employment (not employed, part-time, full time), children (yes, no), and relationship to the participant.

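### Section 14.3 gives the pilot's between-arm differences a part in choosing and powering the definitive trial's primary outcome, which about 24 participants per arm cannot support

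*Protocol*

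**What the plan says.** Three places in the protocol bear on this.

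- **Section 14.3** states the analysis: "Between-arm differences, including in changes from baseline, will be reported for the patient-reported outcomes with corresponding measures of dispersion". It gives the purpose in the same sentence: "to enable an assessment of sensitivity to change to inform primary outcome selection for a definitive trial and a formal power calculation for this outcome". No other source for the definitive trial's target difference is named.
- **Section 14.1** (repeated in section 6) gives three aims for the 60 participants: operational experience, estimates of the feasibility outcomes, and "to estimate the variability of the proposed patient outcomes to inform a future sample size calculation". The numerical justification is the precision of the 12-week retention rate.
- **Section 12.1** describes the mechanism measures by their link to "health-related quality of life (as the proposed outcome for a definitive trial". It gives neither an instrument nor a time point. The outcome row of the progression criteria (Figure 2) rests on EQ5D completeness at 12 weeks.

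Section 7.6 lists six patient-reported measures, collected at baseline, intervention end and 12 weeks: EQ-5D-5L, Barthel Index, Nottingham Extended Activities of Daily Living, Short Falls Efficacy Scale-International, pain rating and New Mobility Score.

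**The concern.** A pilot of this size can give a usable, if imprecise, estimate of an outcome's spread. Its estimate of a treatment effect is mostly sampling error. Section 14.3 gives the effect estimates two tasks, helping to pick the primary outcome and feeding its power calculation, and section 14.1 does not size the pilot for either.

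The section also reopens a choice that section 12.1 treats as provisionally made. If another measure were preferred because it happened to separate the arms more, the progression criterion would have tested the completeness of an outcome that is no longer primary.

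Secondary objective 7, the indicative sample size, is at stake. An observed difference used as the target carries the pilot's noise into the definitive trial, and choosing the outcome with the largest difference biases that target upwards.

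**Working it through.** **Inputs from the protocol.** 60 participants, 30 per arm, and 80% retention (section 14.1); 1:1 allocation (section 7.4); six candidate measures (section 7.6).

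**Assumptions, because the protocol gives no figures.** Outcomes in SD units, with benefit taken as positive; a definitive trial at two-sided 5% and 80% power; true effects of 0.2 or 0.3 SD; correlation between outcomes from 0 to 0.7; one time point only.

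**1. The plan's own figures reproduce.** For 48/60 the exact 95% interval is 67.7% to 89.2%, a half-width of 10.8 points (stated: ±11%). Follow-up data: 30 × 0.80 = 24 per arm (stated: about 24).

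**2. Precision of one difference.** SE = √(2/24) = 0.289. The 95% half-width is 1.96 × 0.289 = 0.57 SD. For a change score the SE is multiplied by √(2(1 − r)). In units of the raw SD the half-width is then 0.44 at a baseline correlation r of 0.7 and 0.80 at r = 0. The pilot's power to detect 0.2, 0.3 or 0.5 SD is 10%, 18% or 41%.

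**3. Largest of six when nothing differs.** The expected maximum of six independent standard normal values is 1.267. With common correlation ρ the mean largest difference is 1.267 × √(1 − ρ) × 0.289:
- ρ = 0: 0.37 SD
- ρ = 0.5: 0.26 SD
- ρ = 0.7: 0.20 SD

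**4. One pre-chosen outcome, sized on its own observed positive difference.** n per arm = 2 × ((1.96 + 0.8416)/d)², where d is the observed difference.
- True effect 0.2: the median positive observed difference is about 0.29. It gives about 187 per arm, where the true effect needs 393. True power = Φ(0.2/√(2/187) − 1.96) = 49%.
- True effect 0.3: the median is about 0.354. It gives about 125 per arm, where the true effect needs 175. True power = Φ(0.3/√(2/125) − 1.96) = 66%.

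Simulation (200,000 runs, keeping observed differences above 0.01 SD) gives median true power of 48% and 65%. It drops the 25% and 16% of pilots with no such difference.

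**5. Sized on the largest of six** (same simulation, nominal 80% power). The last column takes one outcome at 0.3 SD and five at 0.2 SD; chance is 17%.

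| ρ | Largest ≥ 0.3 SD with no true effect | Median true power, all effects 0.2 | Median true power, all effects 0.3 | Best outcome picked |
|---|---|---|---|---|
| 0 | 62% | 17% | 25% | 25% |
| 0.3 | 51% | 20% | 29% | 27% |
| 0.5 | 43% | 22% | 32% | 29% |
| 0.7 | 35% | 26% | 38% | 33% |

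**6. What the pilot can give.** A pooled SD on 46 df has a 95% interval of 0.83 to 1.26 times its estimate. The one-sided upper 80% limit is √(46/37.8) = 1.10 times the estimate. This is imprecise, but the imprecision can be stated and allowed for.

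**The case against.** The strongest reply is that section 14.3 can be read harmlessly. Its differences are only to inform the choice. They are reported with measures of dispersion, and dispersion is the very input that section 14.1 names for the future sample size. Section 12.1 already proposes an outcome, objective 7 asks only for an indicative sample size, and completion rates and acceptability are to be assessed anyway. If only the SD were carried forward, selection bias in the effect would not arise.

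Much of this stands, and it rules out several stronger readings:

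- A reader might infer that the measure with the largest difference will be chosen and its difference adopted as the target, so that the definitive trial is bound to be underpowered. The protocol says neither. Steps 4 and 5 show what would follow from such use, not what is planned.
- A reader might take section 14.1 as sizing the pilot for variability alone. It gives three aims, and its calculation concerns retention.
- A reader might take section 12.1 as fixing EQ-5D-5L at 12 weeks. It names only the concept.
- A reader might object that the differences are unadjusted. Section 14.3 does not say so, and the model is commonly left to the statistical analysis plan. Change scores also have a natural place in judging sensitivity to change.

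The reply does not remove the stated purpose. Section 14.3 links between-arm differences to outcome selection and to power, excludes no use of them, and offers no other target difference.

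**Conclusion.** The point holds in a limited form. Section 14.3 gives between-arm differences a role that goes beyond section 14.1 and fits poorly with section 12.1, and at about 24 per arm they cannot carry it. The precision figure, ±0.57 SD, follows from the protocol's own numbers. The 0.26 to 0.37 SD for the largest of six null differences rests on an assumed correlation of 0.5 to 0.

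Underpowering is conditional on the observed difference becoming the target. In that case the median true power is about 48% to 65% for one pre-chosen outcome with a positive observed difference, and about 17% to 38% after picking the largest of six. Both ranges assume true effects of 0.2 to 0.3 SD and a nominal 80%. The primary fidelity objective is unaffected.

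**What to change.** Reword the sentence in section 14.3 along these lines:

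- Report between-arm differences descriptively with confidence intervals, and state that they will not be used to select the primary outcome or to set the target difference.
- State that health-related quality of life is the candidate primary outcome, naming the instrument and time point, to be confirmed or changed on completeness, acceptability and floor or ceiling effects.
- Base the power calculation on an externally justified minimum important difference. Take from the pilot the SD with its uncertainty (for example the upper 80% limit, about 1.10 times the estimate), the baseline correlation and retention.

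The cost is one paragraph and no new data. Using the upper limit for the SD makes the indicative sample size larger by a factor of about 1.10² = 1.21.

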## **14.4 Progression criteria**

To mitigate the risk of ongoing uncertainty at the end of the feasibility trial, we propose progression criteria outlined in Figure 2.

### **Figure 2: Progression criteria**

|                          | GO                                                              | AMEND                                                             | STOP                                                            |
|--------------------------|-----------------------------------------------------------------|-------------------------------------------------------------------|-----------------------------------------------------------------|
| Recruitment       | ≥40% eligible                                                   | 21-39% eligible                                                   | ≤20% eligible                                                   |
| Recruitment       | ≥50% eligible recruited                                         | 31-49% eligible recruited                                         | ≤30% eligible recruited                                         |
| Randomisation     | ≥70% of those recruited randomised                              | 49-70% of those recruited randomised                              | ≤48% of those recruited randomised                              |
| Fidelity          | ≥80% sessions included all intervention components as described | 51-79% sessions included all intervention components as described | ≤50% sessions included all intervention components as described |
| Outcome, 12-weeks | ≥80% completeness of EQ5D at 12-week follow-up                  | 51-79% completeness of EQ5D at 12-week follow-up                  | ≤50% completeness of EQ5D at 12-week follow-up                  |

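### Figure 2 puts a randomisation rate of 70% in both GO and AMEND and, with no rounding rule stated, leaves gaps of under one point between other bands

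*Protocol*

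**What the plan says.** Section 14.4 proposes progression criteria, set out in Figure 2, to limit the uncertainty left when the feasibility trial ends. Figure 2 has five rows, each with a GO, an AMEND and a STOP band.

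- Randomisation: GO "≥70% of those recruited randomised", AMEND "49-70% of those recruited randomised", STOP "≤48% of those recruited randomised".
- Recruitment, share of eligible patients recruited: GO "≥50% eligible recruited", AMEND "31-49% eligible recruited", STOP "≤30% eligible recruited".
- Recruitment, share eligible: AMEND "21-39% eligible", with GO from 40% and STOP at 20% or below.
- Fidelity: AMEND "51-79% sessions included all intervention components as described", with GO from 80% and STOP at 50% or below.
- EQ-5D completeness at 12 weeks: the same three cut-offs as fidelity.

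The protocol gives no rule for rounding the observed percentages and none for a result that falls on or between the printed edges.

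**The concern.** Progression bands should give one verdict for every possible result, so that the reading of the trial is fixed before the data are known. The Randomisation row fails this at 70%, where GO and AMEND both apply. As printed, the table also gives no verdict for an unrounded result between two whole-number edges.

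In either case the verdict would be settled after the result is seen, by a rounding choice or by argument. Two of the affected rows matter most: the share of eligible patients recruited, where one gap separates AMEND from STOP, and fidelity, which is the primary objective (Section 4).

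**Working it through.** The cut-offs are chosen values, so there is no calculated figure in the plan to reproduce. The check is whether each row returns exactly one verdict for every possible percentage.

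**Step 1. Limits as printed in Figure 2**

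| Row | STOP up to | AMEND | GO from | In two bands | In no band (unrounded) |
|---|---|---|---|---|---|
| Eligible | 20 | 21 to 39 | 40 | none | 20–21, 39–40 |
| Eligible recruited | 30 | 31 to 49 | 50 | none | 30–31, 49–50 |
| Randomised | 48 | 49 to 70 | 70 | 70 | 48–49 |
| Fidelity | 50 | 51 to 79 | 80 | none | 50–51, 79–80 |
| EQ-5D | 50 | 51 to 79 | 80 | none | 50–51, 79–80 |

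The no-band intervals exclude their end points. The double verdict occurs in one row only.

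**Step 2. Whole-percent reading.** Classifying every whole percentage from 0 to 100 leaves no gap in any row. The overlap at 70% remains. Under rounding, any rate from 69.5% to just under 70.5% becomes 70% and falls in both bands. It is reachable at the planned size: with 60 randomised (30 per arm, Section 14.1) out of 86 recruited, 60/86 = 69.8%, which rounds to 70%.

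**Step 3. Unrounded reading.** Reachable results with no verdict include:

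- *Eligible recruited*, taking 60 recruited: 60/194 = 30.9% to 60/199 = 30.2%, neither AMEND nor STOP; 60/121 = 49.6% and 60/122 = 49.2%, neither GO nor AMEND.
- *Eligible*, taking the 255 admissions in 2022 (Section 14.1) as an illustrative denominator: 100/255 = 39.2% and 101/255 = 39.6%, neither GO nor AMEND.
- *Randomised*, taking 60 randomised: 60/123 = 48.8% and 60/124 = 48.4%, neither AMEND nor STOP.
- *Fidelity*, with an assumed number of sessions because the protocol gives none: 119/150 = 79.3% and 159/200 = 79.5%, neither GO nor AMEND.
- *EQ-5D* with a denominator of 60: no gap is reached, since 47/60 = 78.3% and 48/60 = 80.0%, and 30/60 = 50.0% and 31/60 = 51.7%.

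**Step 4. How likely is a fidelity result in the 79–80% gap?** This needs two assumptions that the protocol does not supply: the number of sessions and the true fidelity. Treating sessions as independent, the binomial probability of a result strictly between 79% and 80% is:

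| True fidelity | 120 sessions | 150 sessions | 200 sessions |
|---|---|---|---|
| 70% | 0.7% | 0.3% | 0.1% |
| 80% | 8.7% | 7.9% | 6.9% |
| 85% | 2.1% | 1.4% | 0.8% |

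The chance is appreciable only when true fidelity is close to the GO limit.

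**Step 5. Contiguous bands.** Keep each GO and STOP limit and let AMEND be everything strictly between. Every result x/N for N from 1 to 399 then gives exactly one verdict in all five rows, with no exceptions.

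**The case against.** The strongest defence is that the table is written in whole percentages. AMEND starts exactly one point above STOP in all five rows, which is how whole-percent bands are normally set out. On that reading there are no gaps, and a rounding convention is the sort of detail a statistical analysis plan can hold. This largely stands, and it is why the gaps are the secondary part of the point. It does not rescue the Randomisation row, because the overlap at 70% survives rounding and is widened by it.

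It can also be said that, on unrounded percentages, the overlap cannot be reached with 60 randomised: 60/85 = 70.6% and 60/86 = 69.8%, and no whole number of recruits gives exactly 70%. That is correct. But the unrounded reading is the one that opens the gaps. Neither reading gives a table with exactly one verdict throughout.

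Three stronger readings are tempting, and the protocol does not support them.

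- A reader might infer that recruitment and fidelity can also return two verdicts. They cannot; their only defect is a missing verdict on the unrounded reading.
- A reader might infer that the 30–31% gap sits next to the sponsor's own planning rate of 32%. Section 6 gives that rate for patients both eligible and invited, whereas the Figure 2 row is worded for eligible patients. Sections 7.2 and 14.3 count eligible and approached patients separately, so the rate cannot be carried over.
- A reader might infer that Figure 2 mechanically decides whether the definitive trial proceeds. Section 14.4 only proposes the criteria and states no automatic rule.

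**Conclusion.** The point holds in a limited form and is minor. The overlap at 70% in the Randomisation row is an error on the face of the table, out of line with the other four rows, and it does not depend on any assumption. The gaps exist only if results are read unrounded, and each is less than one percentage point wide. They matter because no rounding rule is stated, and one of them touches the primary objective.

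The examples rest on 60 recruited or 60 randomised as labelled, on 255 as an illustrative denominator, and on assumed session counts. The fidelity probabilities also rest on an assumed true rate and on independent sessions, so they show a range and do not predict a result. None of this calls the cut-off values themselves into question.

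**What to change.** Keep every GO and STOP cut-off, state that bands apply to unrounded percentages, and rewrite AMEND as the open interval between them:

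- Eligible: above 20% and below 40%.
- Eligible recruited: above 30% and below 50%.
- Randomised: above 48% and below 70%.
- Fidelity and EQ-5D completeness: above 50% and below 80%.

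A whole-percent rounding rule alone would not be enough; the Randomisation AMEND band would also have to stop below 70%. The cost is a wording change to one table, made before the results are known, with no effect on thresholds, data collection or participants.
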